## Study objectives

The overall aim of the study is to describe the effectiveness and cost-effectiveness of IG2, RG, and PBO ITNs in comparison to standard pyrethroid-only ITNs. Specific objectives are organized into five study components: (1) malaria epidemiological surveillance to evaluate the impact of dual-AI ITNson malaria burden, (2) entomological surveillance to evaluate the impact of dual-AI ITNs on key entomological outcomes (3) anthropological data to assess how transmission risk is influenced by human behaviours, (4) assessment of the chemical and physical durability of the new ITN types, and (5) evaluation of the cost and cost-effectiveness of dual-AI ITNs.The epidemiological objective is to evaluate the effectiveness of IG2, RG, and PBO ITN distributions, compared to standard pyrethroid-only ITN mass distributions, in reducing:Malaria prevalence measured during annual cross-sectional surveys in children 6 months to 5 years (Burkina Faso, Mozambique, and Nigeria) and all ages (Rwanda).Passive malaria case incidence rates measured using routine surveillance systems (DHIS2).The entomological objective is to compare post-ITN distribution trends in vector densities, human biting rates, and entomological inoculation rates using CDCLTs and HLCs and to establish baseline. In addition, entomological objective is to evaluate insecticide susceptibility patterns in the primary vector species populations.The anthropological objective is to assess how human behaviour influences exposure risk and understand the key drivers of ITN use and non-use behaviour across districts with different types of ITN types.The ITN durability monitoring objective is to assess the attrition, survivorship, physical integrity, and insecticidal bioefficacy of all ITN types at baseline, 12 months, and 24 months.The cost-effectiveness objective is to combine data on product effectiveness (based upon case incidence rates measured for objective 1) and data on product prices and costs of delivery and deployment to estimate a mean cost per case averted for each ITN type.

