#### Epidemiological surveillance analysis

The trials are planned under a superiority, difference-in-differences (DiD) framework. The comparisons will consist of one-sided tests of the null hypothesis that the outcomes (reductions in parasite prevalence or case incidence rate from baseline to end line) in each intervention district are statistically the same as the outcomes in the appropriate control district control arm.

Malaria infection prevalence, determined by RDT tests during the cross-sectional surveys, will be analysed by an appropriate difference-in-differences model comparing changes in prevalence from year to year across study districts (intervention type). Considering sample size constraints, a single indicator age group will be targeted using a clustered sampling approach, clustering observations at a sub-district level (either by sector, health facility catchment, or village—whichever is most practical). Statistical analysis is done using Stata (version 14.2 or later). A difference-in-differences approach will assess matched-pair comparisons of the mean change in malaria prevalence from year to year, before and after ITN distribution across each study districts (intervention/control) comparison. The approach taken within each evaluation setting is powered independently to compare changes in prevalence observed in the ITN intervention districts to changes in the prevalence observed in the appropriate ITN control district. However, given the proposed study design and sampling frame, secondary post-hoc analyses, with Bonferroni’s correction for multiple comparisons, will likely be able to detect an effect size difference of around 20% between any two ITN types at 24 months. The protective efficacy of dual-AI ITNs is determined by multilevel logistic regression model for each year, adjusted for age and individual ITN use the previous night, with clustering at the district level.

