
The epidemiological data from routine health facilities and annual cross-sectional surveys from the four countries with varying malaria endemicity will be key in providing supporting evidence for broader scale-up and policy. In addition, the anthropological data will enhance understanding of community perceptions of the dual AI ITNs that impact their uptake and use and therefore their effectiveness in vector control. In understanding the reasons for any differences in cost-effectiveness, it is critical to understand ITN impacts on the primary and secondary vector species. The results from the entomological surveillance will also provide key evidence on the temporal and spatial patterns of vector species distributions, entomological inoculation rates, and mosquito mortality in the short to medium terms for IG2 and RG, as compared to pyrethroid ITNs or other PBO ITNs in settings where insecticide resistance is high. Evidence from physical and insecticidal durability monitoring will provide NMCPs with key information on the performance and estimated useful life of the different ITN types under different conditions and across countries, which will in turn influence their cost-effectiveness and timing of replacement net distribution. Finally, data from each component of the study will be available to inform mathematical modeling work designed to help describe and predict the effectiveness and cost-effectiveness of different net types in various malaria transmission settings and intervention contexts across sub-Saharan Africa.

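### The yearly protective-efficacy model adjusts for net use the previous night, a post-distribution variable, so it does not estimate the total effect of the distributions

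*Protocol article*

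**What the plan says.** The section on epidemiological surveillance analysis describes two analyses of survey prevalence.

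- The main one. Prevalence by RDT "will be analysed by an appropriate difference-in-differences model comparing changes in prevalence from year to year across study districts". No net-use covariate is stated for it.
- A second, at the end of the same paragraph: a multilevel logistic regression, fitted separately for each survey year, that yields the protective efficacy of the dual-AI nets. Its covariates are stated in these words: "adjusted for age and individual ITN use the previous night". The district is named as the level of clustering.

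The epidemiological objective (Study objectives) is to "evaluate the effectiveness of IG2, RG, and PBO ITN distributions, compared to standard pyrethroid-only ITN mass distributions".

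Two other places bear on the role of net use. The anthropological objective is to "understand the key drivers of ITN use and non-use behaviour across districts with different types of ITN types". The Discussion says the anthropological data will improve understanding of "community perceptions of the dual AI ITNs that impact their uptake and use and therefore their effectiveness in vector control".

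Use is one of the items in the household questionnaire given at each cross-sectional survey (the text under Exclusion). The ethics section adds that a household need not have received a campaign net to take part.

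**The concern.** An objective about distributing one product rather than another asks for a total effect: everything that follows from the choice of product, including whether people keep the net and sleep under it. If net type alters use and use alters infection, use is a mediator. Holding it constant takes that route out of the net-type coefficient.

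Last-night use may also respond to how many mosquitoes people notice, which is itself related to infection. Conditioning on use can then open a non-causal path between net type and infection.

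At stake is the survey-based efficacy figure reported for each year. Read as the effect of the distribution, it could be too low or too high, by an amount that may differ between products and between years as nets wear.

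**Working it through.** **Step 1: does the covariate follow the intervention?** Table 3 gives yearly surveys, and use is asked at each. In all follow-up rounds it is therefore measured after the campaign.

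**Step 2: does the protocol treat use as a consequence of net type?** The Discussion sentence runs from perceptions of the dual-AI nets, to uptake and use, to effectiveness. The anthropological objective is weaker evidence: it sets out to learn what drives use across districts with different nets and does not assert a difference. The Durability monitoring section adds that retention and physical integrity may differ by product, a second possible route to use.

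**Step 3: does the model match the objective?** The objective is the effect of distributions. The model gives the net-type contrast at a fixed level of current use. The two coincide only if use does not depend on net type, apart from the non-collapsibility of the odds ratio.

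**Step 4: how large could the gap be?** The protocol has no figure to reproduce. It gives neither use by district nor an odds ratio for use, so every input here is an assumption:

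- prevalence in non-users with the standard net: 30% or 50%
- odds ratio of infection for use: 0.4, 0.6 or 0.8
- odds ratio for net type at fixed use: 0.70, so use-adjusted efficacy = 1 − 0.70 = 30%
- use, standard versus dual-AI district: 70/60, 70/70, 70/80 or 60/80%

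Model: logit P(infection) = a + log(OR_use) × use + log(OR_net) × net type. Prevalence in a district = u × P(users) + (1 − u) × P(non-users). Total efficacy = 1 − (odds in the dual-AI district ÷ odds in the standard district).

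One case in full, with 30% prevalence in non-users, OR_use 0.4 and use 70/80%:

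- Standard net. Non-user odds 0.30/0.70 = 0.4286. User odds 0.4 × 0.4286 = 0.1714, probability 0.1463. Prevalence 0.7 × 0.1463 + 0.3 × 0.30 = 0.192, odds 0.2383.
- Dual-AI net. Non-user odds 0.7 × 0.4286 = 0.30, probability 0.2308. User odds 0.7 × 0.1714 = 0.12, probability 0.1071. Prevalence 0.8 × 0.1071 + 0.2 × 0.2308 = 0.132, odds 0.1519.
- Total odds ratio 0.1519/0.2383 = 0.637, efficacy 36.3%, against 30% adjusted.

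Range over the six combinations of prevalence and OR_use:

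| Use, standard / dual-AI | Use-adjusted efficacy | Total efficacy |
|---|---|---|
| 70% / 60% | 30% | 21.9–28.3% |
| 70% / 70% | 30% | 29.0–30.0% |
| 70% / 80% | 30% | 31.5–36.3% |
| 60% / 80% | 30% | 33.0–42.1% |

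The shift of at most 1 point with equal use is non-collapsibility of the odds ratio, not mediation.

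**The case against.** **Confounding is the strongest objection.** Districts were not randomised. The protocol acknowledges fundamental differences between them, and Table 2 shows different campaign dates within Burkina Faso and within Rwanda. Use may differ for reasons unrelated to product, and a model fitted year by year has no baseline differencing to absorb this. Adjusting for use is then an understandable attempt to isolate the product, and dropping it trades one possible bias for another. This stands in part. It supports adjusting for factors that precede distribution or that net type cannot change, and reporting both versions. It does not make a post-distribution variable suitable for defining the programme effect.

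**Net types may be hard to tell apart.** The Study design section says they are not always distinguishable by size, shape or colour, which could limit differences in use driven by perception. That bears on size, not on whether the estimate matches the objective.

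**The article is condensed.** It refers to a data analysis framework that is not shown. The absence here of a use-unadjusted version is therefore no fault in itself; the point rests on the adjustment that the article does state.

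A reader might also infer more than the documents support:

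- That the main effectiveness analysis is affected. The evaluations are framed and powered on the difference-in-differences comparison, for which no use covariate is stated.
- That cost-effectiveness is affected. It rests on case incidence from routine data, or on transmission modelling. The incidence model is described at health-facility level, with rainfall and catchment population as likely covariates.
- That adjustment always removes part of the effect. The direction depends on which net is used more, and no use figures are given.
- That adjustment discards community-wide mosquito killing. No interaction between net type and use is stated, so the net-type coefficient applies to users and non-users alike and keeps that protection.

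**Conclusion.** The point holds for one analysis. As described, the yearly protective-efficacy model estimates an effect with current use held constant, while the objective asks for the total effect of the distributions. The protocol's own account of use as a link between net type and effectiveness is enough to establish the mismatch.

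Its size cannot be determined from the documents. Under the assumed inputs, a stated efficacy of 30% could stand for a total effect anywhere from about 22% to 42%, and for nearly the same value if use is equal. Those limits depend on use gaps of 10 to 20 points and on the assumed strength of protection from use. The change is worth making because the sign of the bias is unknown in advance and may differ by product and year.

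**What to change.** - Take the programme-effect estimate from the yearly protective-efficacy model **without** current net use. Adjust for age and for questionnaire variables that net type does not change: house structure and socio-economic variables.
- Where available, add net use from the baseline survey. New households are drawn each round, so this must be an aggregate. Cluster level is preferable, if the same villages are revisited: Table 1 has one district per net type in each evaluation (Rwanda adds a standard-net district with IRS), so a district value cannot be separated from net type in a two-district comparison and would be reported descriptively. Tables 2 and 3 also limit where baseline use is truly pre-distribution: in Burkina Faso the PBO campaign was complete in June 2019 and the first survey was in July 2019.
- Keep the use-adjusted or use-stratified model as a secondary analysis, labelled as a direct effect with use held constant.
- Report both each year, with use by net type beside them, so that readers can see whether a gap between the two estimates goes with a difference in use.

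The cost is a changed covariate list and one extra fitted model per year, with no new data. The downside is that the use-unadjusted estimate may carry some confounding from pre-existing differences in use, which is the reason to show both.

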### Epidemiological component

Across all countries, malaria burden is measured through cross-sectional surveys, routine health facility data, and in most evaluations, antenatal care surveillance. For all countries, the study aims to conduct all surveys during high transmission seasons. This is complicated in many areas because of seasonal rains that impact operations. In addition, because of the timing of the grant and the net distribution, with the necessity to conduct a baseline survey before or contiguous with distribution, the timing of baseline surveys were adjusted in Rwanda, Nigeria, and Mozambique. Efforts are made to ensure that the post distribution cross-sectional survey timing is within a higher transmission season and is consistent across the years for comparison. In Burkina Faso, where four rounds of SMC are done annually in children 3 months to 5 years during the malaria transmission season, the study aims to time the surveys before SMC campaigns to ensure that the measurements are not conflated with the effects of the first round of seasonal malaria chemoprevention.

In each study district, villages were randomly selected for participation using probability proportionate to size, from which households were sampled either randomly or following a standard systematic sampling approach (e.g., every third household) During each survey a new set of households with eligible participants are selected (Table 3).

**Table 3 Tab3:** Cross-sectional survey methodology by country

Country	Participants		Sample size (households)	Survey months
	Questionnaire	Prevalence		
Burkina Faso	Household head or primary caregiver	Child aged 6 to 59 months	570 per year (2280 total)	• July 2019 • July 2020 • July 2021 • July 2022
Northern and western Mozambique	Household head or primary caregiver	Child aged 6 to 59 months	2520 per year (7,560 total)	• September–October 2020 • September–October 2021 • August–September 2022
Nigeria	Household head or primary caregiver	Child aged 6 to 59 months	1680 per year (5,040 total)	• September 2020 • November 2020 • November 2021
Rwanda	Household head or primary caregiver	All household residents aged 6 months and older	450 per year (1,800 total)	• February 2020 • December 2020 • November 2021 • November 2022

*LGA* local government area

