### Exclusion

The exclusion criteria for cross-sectional surveys are as follows:Households with no children within the target age group will be excluded for each country.Households or individuals who did not provide informed consent or assent.Households with children in the age group but are not resident in the village for at least six months.

Participants present at the time of the house visit are tested for malaria by conventional malaria rapid diagnostic test (RDT) and those with a positive RDT are treated following national malaria treatment guidelines [21–24]. A questionnaire is administered to each head of house or representative to collect data on demographic characteristics of household members, house structure, socio-economic variables, care-seeking behaviour and ITN indicators including the ITNs per house, ITN ownership and utilization at night.

Passive surveillance of malaria cases comes from routine health facility data collected during outpatient health facility visits or from community health workers in each study district. Analysis of routine malaria health management information system data starts approximately one year prior to ITN campaigns. In addition, in Nigeria, Western Mozambique, and Burkina Faso, data on the prevalence of malaria infection is assessed from pregnant women attending their first antenatal care visits in selected health facilities. Data quality assessments are conducted in some countries to assess the quality and completeness of malaria surveillance data. Table 3 details the similarities and differences in cross-sectional survey methods used in each country.

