Routine health facility data provide real time insight to malaria cases and trends, but are often limited by poor data integrity, limited capacity for quality control, and supply shortages, leading to underestimation of true malaria case incidence rates. However, this robust multi-country protocol aims to ensure that the breadth of information and multiple methods of evaluation will strengthen conclusions on the cost-effectiveness of these interventions across a variety of settings in a way that a single evaluation or single measure could not.

Another source of variability, and a limitation of the study design particularly important when considering preliminary and interim results, is the relatively brief periods that were available for baseline, pre-intervention data collection given the need to align study activities with already existing regional and national-level universal coverage campaigns. The timing of campaign activities differed across study districts and so does the resulting length of time that each intervention has been deployed to date.

Due to the complexity of national malaria programming and each net distribution campaign, the protocols are not identical; however, the key ITN indicators have been harmonized across studies. A single data analysis framework has been codeveloped by study partners and is supplemented by local nuance for each individual analysis, including possibilities such as duration of net ownership, differences in measured baseline characteristics, and data gaps. In each case, if there is deviation from the main analysis plan, these actions will be described.

It is also worth noting these NNP pilot studies are not able to estimate the general impact of any (or all) ITNs relative to no ITNs, and instead they are attempting to quantify the incremental impact of dual-AI ITN types relative to standard, pyrethroid-only ITNs that still provide protection from malaria—particularly when access and use are high.

Finally, all these operational challenges were exacerbated by the ongoing COVID-19 pandemic response, and steps to account for these changes will be contextualized for during any final analysis.

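### The yearly survey efficacy model compares non-randomised districts with no baseline term and adjusts only for age and net use, though housing and socio-economic data are collected

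*Protocol article*

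**What the plan says.** The Epidemiological surveillance analysis section describes two analyses of survey prevalence.

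- **Difference-in-differences.** Prevalence "will be analysed by an appropriate difference-in-differences model comparing changes in prevalence from year to year across study districts". No covariates are listed for this model.
- **Protective efficacy.** The text describes this estimate as "determined by multilevel logistic regression model for each year". The adjustment is then given: "adjusted for age and individual ITN use the previous night". The grouping term in the model reads "with clustering at the district level". Here a covariate set is stated, and it has two members.

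On data collection, the Exclusion subsection of the Epidemiological component says: "A questionnaire is administered to each head of house or representative to collect data on demographic characteristics of household members". The same sentence goes on to list "house structure, socio-economic variables, care-seeking behaviour and ITN indicators". The Epidemiological component adds: "During each survey a new set of households with eligible participants are selected".

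On allocation, the section on identifying study districts says that the national programmes, with partners and donors, decided which net went where. The Discussion concedes that districts may differ in fundamental ways and that baseline burden varied substantially. It also says that the common analysis framework may be supplemented locally, and among the possibilities it mentions "differences in measured baseline characteristics". It names no variable and makes no commitment.

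**The concern.** A model fitted within one follow-up year cannot separate what the net did from what the district was like beforehand. In a randomised design the allocation deals with that; here it does not. The district-level clustering term does not help either, because within each setting of Table 1 each new net type has one district, so net type and district coincide.

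Housing quality and household wealth are plausible determinants of malaria infection and are unlikely to be altered by the type of net handed out. Adjusting for them should therefore not remove any of the net effect. They are already on the questionnaire. The routine-data model in the same section does provide for possible confounders, with rainfall and catchment population as examples. The survey efficacy model makes no such provision, although survey prevalence is the outcome on which the evaluations are powered.

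At stake is a published protective-efficacy figure for each net and year that partly reflects which district had better houses. Leaving adjustment to local choice also allows the covariate set to be settled after the data are seen.

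**Working it through.** The plan states no figure that this point could reproduce. The check is a reading of the model followed by an illustration.

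**1. What each model removes.**
- Yearly model: the net coefficient is district A against district B in year t. A fixed housing difference between A and B stays in it unless housing is a covariate.
- Difference-in-differences: the contrast is (A at follow-up − A at baseline) − (B at follow-up − B at baseline). A fixed housing difference with a stable effect cancels.

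The stated two-covariate list belongs to the first model, and that is where standing differences matter.

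**2. Standing differences before the nets (Table 1).** Odds ratio = [p₁/(1−p₁)] / [p₀/(1−p₀)], new-net district against control:
- Banfora 13.8% v Gaoua 32.4%: (0.138/0.862)/(0.324/0.676) = 0.33
- Guro 47.6% v Chemba 29.4%: (0.476/0.524)/(0.294/0.706) = 2.18
- Changara 29.4% v Chemba 29.4%: 1.00

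Table 1's footnote says that these surveys were not done at study-area level, so the figures are only indicative. They show that pre-existing gaps can be large and can run in either direction. They do not show how much of a gap is due to housing or wealth.

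**3. Illustration for the yearly model.** Assumptions, none of them from the documents: 50% of houses improved overall; odds ratio for infection, improved v not, 0.5 to 0.7; standing difference in improved share between districts 5 to 20 points. From the documents: Gurue prevalence 44.3%, and planned reductions of 15% and 5%.
- Stratum prevalences averaging 44.3%: at OR 0.5, 52.8% and 35.8% (gap 16.9 points); at OR 0.7, 48.7% and 39.9% (gap 8.8 points).
- Movement of the contrast = gap × difference in share. For 5 points: 0.05 × 8.8 = 0.4 to 0.05 × 16.9 = 0.8. For 20 points: 0.20 × 8.8 = 1.8 to 0.20 × 16.9 = 3.4.
- Planned extra effect: 44.3 × (0.15 − 0.05) = 4.4 points.
- On the model's own scale, take 60% v 40% improved and no net effect. Prevalences are then 42.6% v 46.0% at OR 0.5 (apparent odds ratio 0.87), or 43.4% v 45.2% at OR 0.7 (0.93). The planned contrast is 37.7% v 42.1%, an odds ratio of 0.83.

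**4. Chance shifts in household mix between rounds.** With 2520/6 = 420 households per district-round (equal split assumed) and design effect 1:
- SE of the difference-in-differences in a 50% household characteristic = 2√(0.25/420) = 4.9 points.
- Its contribution to prevalence is 4.9 × 0.088 to 4.9 × 0.169 = 0.4 to 0.8 points.
- SE of the prevalence difference-in-differences = √(4 × 0.443 × 0.557/420) = 4.8 points.
- Share of outcome variance explained by housing = gap² × 0.25/(0.443 × 0.557) = 0.8% to 2.9%.
- SE reduction from adjusting = 1 − √(1 − share) = 0.4% to 1.5%, if design effects are similar for housing and infection.

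**The case against.** Two stronger readings are tempting, and the documents support neither.

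- **That the difference-in-differences also leaves these variables out.** Its covariates are not listed. A journal article commonly leaves that to an analysis plan, and the plan is not shown, so silence is not evidence of omission. Nor does any passage suggest that household mix will drift differently between districts; the sampling method described is the same at each round.
- **That chance changes in the sampled households bias the result.** A 10-point differential shift in improved housing would, on the assumptions above, move the difference-in-differences by 0.9 to 1.7 points, which is 20 to 38% of 4.4. That is not a measure of bias. Villages are drawn at random with probability proportional to size, and households randomly or systematically, so such shifts are sampling error and belong in the standard error. Adjusting for them buys only the small precision gain in step 4.

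The other side also notes that the Discussion admits confounding and leaves room to adjust for measured baseline differences. That is fair, but it is optional, local and names no variable, whereas the efficacy model's covariate set is stated outright. Finally, household covariates cannot repair a design with one district per new net type in each setting. That stands, and it limits what the fix can deliver.

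**Conclusion.** The point holds for the yearly protective-efficacy model. As described, that model contrasts non-randomised districts within a year without a baseline term, and its two covariates leave standing housing and wealth differences in the estimate. The relevant data are already collected.

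The size is unknown, because the documents give neither the district distribution of these variables nor their association with infection. The illustration (0.4 to 3.4 points against a planned 4.4) rests wholly on assumed inputs. The true movement could be near zero and could favour either net. No bias is claimed for the difference-in-differences. This is an inexpensive improvement, and it would not make the yearly estimate free of confounding.

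**What to change.** In the Epidemiological surveillance analysis section:

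1. Add house structure and a socio-economic index, built from the survey questionnaire, to age in the yearly efficacy model. This point takes no position on whether previous-night net use stays in.
2. Use the same set in an adjusted version of the prevalence difference-in-differences, so that the two analyses can be compared.
3. Report unadjusted and adjusted estimates side by side.
4. Tabulate these variables by district and survey round.
5. State that adjustment for household variables cannot remove unmeasured district-level confounding.

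The cost is a few lines of analysis wording and one extra model per comparison, with no new data collection. The downside is a small loss of records with missing socio-economic items.
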